### Sample size/power calculation

The aim of the study is to compare the effectiveness of the intervention against TAU using a cox regression survival analysis with a significance level of 5%. Based on previous studies of depression incidence in chronic back pain patients and subclinical depression, we expect a mean incidence of MDD of 20% in the control group within the 12-months follow-up period [52–55]. Based on a prior conducted trial, we assume an absolute risk reduction of 9% with a respective hazard ratio of 0.522 between treatment and control group at 12 months after randomization [34]. A total of 64 events (event = onset of depression) need to be observed to detect a 47.8% decrease in hazard (hratio = 0.522) of the treatment group relative to the hazard of the control group based on a power of 80%. Accordingly, 406 participants (203 per group) need to be randomized (calculated using Stata/SE 13.1). The inclusion of relevant baseline predictors of depression onset will further increase power (e.g. baseline depression severity). Recruitment will be continued to allow for an expected attrition rate of 20%.

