## Statistical analysis

### Clinical analyses

All analyzes will be performed according to the intention-to-treat (ITT) principle. Kaplan-Meier curves and Cox proportional hazard regression analysis will be used to determine differences in time to onset of MDD in weeks between both study conditions over a follow-up period of 12 months. The dependent variable will be time to onset of MDD and treatment condition will be the independent variable. The proportional-hazards assumption will be tested based on the scaled Schoenfeld residuals test. Survival analysis assumes that censoring (i.e., a participant is lost-to-follow-up or completes the follow-up period without experiencing a major depressive episode) is non-informative. Non-informative implies that the reasons why participants drop out of the trial are unrelated to the study condition (i.e., participants in one study arm should not be routinely censored). We will apply the following methods to deal with informative censoring, if necessary: (a) imputation techniques for missing data, (b) sensitivity analyses to illustrate best and worst case scenarios to test the robustness of the base case findings and (c) the use of the drop-out event as a study end point [87]. In addition, the number needed-to-treat (NNT) to prevent one additional event in the intervention group versus the control group will be calculated [88]. Covariates will first be checked whether they are associated with the primary outcome, if not left out of the final analysis.

Secondary outcomes will be analyzed using hierarchical linear modeling. To examine potentially moderating covariates, correlation of covariates and outcome parameter are analyzed using multiple regression models. In addition, per protocol analysis will be performed to investigate the influence of drop-outs on study results. Missing data will be imputed using multiple imputation. Potential confounding factors between source population and study population will be assessed, which enables us to evaluate the external validity of the sample. Finally, characteristics of dropped out participants at follow-up will be inspected and resulting socio-demographic differences between intervention and control group will be described. A significance level of *p* ≤ .05 will be set for all analyses.

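### If the best/worst-case scenarios are opposite-arm extremes, then at the plan's own 20% TAU incidence and 20% attrition they cannot tell a robust benefit from a fragile one; a graded tipping-point analysis could

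*Protocol article*

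**What the plan says.** Under Statistical analysis, Clinical analyses, the article notes that the survival analysis assumes non-informative censoring. It lists three methods to be used if that assumption is in doubt: imputation, "sensitivity analyses to illustrate best and worst case scenarios to test the robustness of the base case findings", and drop-out as an end point. It does not state which outcome a lost participant receives in each arm, when an assigned onset is placed, or how the result is read. A significance level of p ≤ .05 "will be set for all analyses".

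The section Sample size/power calculation supplies the figures that decide how such scenarios behave:

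- TAU incidence: "we expect a mean incidence of MDD of 20% in the control group within the 12-months follow-up period".
- Effect: "we assume an absolute risk reduction of 9% with a respective hazard ratio of 0.522", so 11% in the intervention arm.
- Loss: "Recruitment will be continued to allow for an expected attrition rate of 20"%.

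Under Assessments, the SCID is given only at baseline and 12 months. The PHQ-9 is also collected at 9 weeks and 6 months (Table 1).

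**The concern.** Onset is dated retrospectively at the 12-month interview, so a participant who misses that interview has no SCID-based outcome for the whole year. The handling of these participants therefore carries weight.

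Under opposite-arm extremes with 20% loss, the onsets assigned to the arm set to fail outnumber those observed in it: 41 against about 18 (intervention) or 32 (TAU). The sign of the comparison then depends mainly on how many were lost. A true benefit would fail the worst case, and an ineffective programme would pass the best case. Neither result shows how far drop-out must depart from the censoring assumption before the conclusion changes, which is what a robustness check should show.

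**Working it through.** **The plan's own figures.** HR = ln(0.89)/ln(0.80) = 0.522, as stated. The plan says "A total of 64 events (event = onset of depression) need to be observed", "based on a power of 80"%, "using a cox regression survival analysis with a significance level of 5"%. Freedman's formula with a one-sided 5% level gives (1.645 + 0.842)² × (1.522/0.478)² = 62.7 events. Rounded up per arm, that is 32 + 32 = 64. At a mean event probability of (0.20 + 0.11)/2 = 0.155 this needs 404.5 participants, or 203 + 203 = 406. The figures reproduce; the sidedness is a separate matter and does not affect this point.

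**Assumption.** Worst case: all lost intervention participants have an onset and all lost TAU participants have none. Best case: the reverse. Loss is equal in both arms.

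**General result.** Let pI and pC be the 12-month risks among those observed, and a the proportion lost per arm. The worst-case risk difference is

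(1 − a)(pI − pC) + a.

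It is negative (favours the intervention) only if pC − pI > a/(1 − a). At a = 0.20 this requires a reduction above 0.25, which is impossible when pC = 0.20. Solved for attrition, the direction reverses at a = d/(1 + d), where d = pC − pI:

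- design effect: 0.09/1.09 = 8.3%;
- full prevention: 0.20/1.20 = 16.7%.

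**Expected counts, 406 randomised.** Lost per arm: 0.20 × 203 ≈ 41. Observed: 162. TAU onsets: 0.20 × 162 ≈ 32. Intervention onsets: 0.11 × 162 ≈ 18 at the design effect, 32 with no effect, 0 with full prevention. The p values come from a two-sided pooled two-proportion test, z = (difference)/√(2p̄(1 − p̄)/203). For 59 v 32, p̄ = 91/406 = 0.224, SE = 0.0414, z = 0.133/0.0414 = 3.21, p = 0.001.

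| True effect | Worst case (intervention v TAU) | Best case (intervention v TAU) |
|---|---|---|
| None | 73 v 32, p<0.0001, against | 32 v 73, p<0.0001, in favour |
| Design (11% v 20%) | 59 v 32, p=0.001, against | 18 v 73, p<0.0001, in favour |
| Full prevention | 41 v 32, p=0.24, against | 0 v 73, p<0.0001, in favour |

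**If recruitment is inflated for attrition.** 406/0.8 ≈ 508, or 254 per arm with 51 lost. Worst case: 73 v 41 at the design effect (p=0.0007) and 51 v 41 with full prevention (p=0.25). Best case with no effect: 41 v 92 (p<0.0001). The pattern is the same.

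**Cox check.** Simulation with 254 per arm, exponential onset times, 20% loss at uniform times (an assumption) and 150 runs per hazard ratio. The worst case was significant for benefit in 0% of runs at every hazard ratio from 0.1 to 2. The best case was significant for benefit in 99–100% of runs from 0.1 to 1.0.

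**Where the result stops holding.**

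- *Lower loss.* At the design effect with 254 per arm, the worst case is significant for benefit at 2% loss (p=0.03) and not at 3% (p=0.09).
- *Large harm.* The best case was significant in 69% of runs at a hazard ratio of 1.5 and 8% at 2.
- *Higher TAU incidence.* At 35% with full prevention and 254 per arm, the worst case favours the intervention (51 v 71, p=0.04).
- *Same-direction definition.* If all lost participants in both arms count as onsets, 406 randomised gives 73 v 73 with no effect, 59 v 73 (p=0.14) at the design effect and 41 v 73 (p=0.0004) with full prevention. In the 254-per-arm simulation this analysis was significant in 88% of runs at a hazard ratio of 0.25, 41% at 0.522, 3% at 0.75 and 0% at 1.0. It does discriminate.

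**The case against.** The strongest objection is that the article never says the scenarios are opposite-arm extremes. The words also fit a same-direction reading, which does separate strong from weak effects. The definition may be in an analysis plan that is not shown, and leaving it there is no fault in a condensed article. This stands, and it makes the point conditional. In favour of the opposite-arm reading, the section describes informative censoring as drop-out that depends on study arm, and a same-direction worst case would largely duplicate the separate item that treats drop-out as an end point.

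It also stands that the scenarios apply only if needed, carry no decision rule, and sit beside imputation, drop-out as an end point and a per-protocol analysis. However, none of these is described as grading the departure from the censoring assumption.

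A reader might infer that the scenarios have a fixed outcome whatever the treatment effect. The numbers do not support that. The worst case moves from clear harm with no effect to a non-significant difference under full prevention, and the best case loses significance under large harm. Nor do the assigned onsets outnumber all observed ones: 41 is fewer than 18 + 32 = 50 across the trial, and the excess exists only within the arm set to fail. Nor is it right that the trial has no other check on drop-out.

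**Conclusion.** The point holds conditionally, as a cheap improvement. Given opposite-arm extremes, about 20% TAU incidence and about 20% loss in each arm, the expected worst case does not favour the intervention and the best case significantly does, for every true effect from none to full prevention. The pair therefore cannot do the job the plan gives it for a claimed benefit. The margin is wide: at the design effect the worst case changes direction at about 8% loss, against 20% expected. If loss turns out to be only a few per cent, or the scenarios treat both arms alike, the problem disappears. The base-case Cox analysis itself is not affected.

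**What to change.** In Clinical analyses, item (b), make a graded analysis the robustness check:

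- For participants without a 12-month SCID, multiply impute onset from arm, baseline severity and the 9-week and 6-month PHQ-9.
- Multiply their imputed hazard of MDD by a prespecified range of factors (for example 1, 1.5, 2, 3, 4), first in the intervention arm alone, then in both arms.
- Report the factor at which the conclusion changes.
- If extreme scenarios are kept, state what outcome lost participants receive in each arm, label the results as bounds, and do not judge robustness by them.

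The cost is a paragraph of analysis-plan wording and a little programming. No new data are needed, since the PHQ-9 is already scheduled; where it is missing too, the imputation rests on arm and baseline data. The downside is that the range of factors must be chosen in advance.

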#### Covariates

As potentially effect-modifying covariates, demographic variables (gender, age, education), social support and medical variables (prior pain and depression treatments) will be assessed via self-report at baseline. Internet competencies will be assessed by the Internet Affinity Scale [85]. The translated version by Haase and colleagues [86] will be used. Back pain type, severity and chronicity will be extracted from medical records.

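### The stated moderator analysis measures covariate–outcome association, so as written it finds prognostic factors and cannot tell them from effect modifiers

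*Protocol article*

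**What the plan says.** The Covariates section of the protocol article introduces the variables by their purpose: "As potentially effect-modifying covariates, demographic variables (gender, age, education), social support and medical variables". The Assessments section gives them the same label.

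The only method for studying them is in the second paragraph of Clinical analyses, directly after the sentence on hierarchical linear models for the secondary outcomes: "To examine potentially moderating covariates, correlation of covariates and outcome parameter are analyzed using multiple regression models".

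Two sentences in the first paragraph of that section bear on it. The primary Cox model is described without covariate or interaction terms: "The dependent variable will be time to onset of MDD and treatment condition will be the independent variable". And there is a selection rule: "Covariates will first be checked whether they are associated with the primary outcome, if not left out of the final analysis".

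The article nowhere mentions a treatment-by-covariate interaction or a comparison of treatment effects across subgroups.

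**The concern.** The sentence names one target and then a quantity that measures another. Whether a covariate predicts the outcome is a question about prognosis. Whether it moderates the intervention is a question about how the treatment effect changes with the covariate. A strong predictor that acts equally in both arms has no moderating role, yet would be reported as a moderator. A covariate that changes the treatment effect but has little average association with the outcome would be missed.

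The selection rule works in the same direction. It is a prognostic criterion, and if it is used to decide which moderators are examined it tends to discard pure modifiers first.

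At stake is the reading of the moderator results. Patients at higher risk in both arms could be described as patients in whom the intervention works differently.

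**Working it through.** **Inputs from the protocol article (Sample size/power calculation).** 406 participants, 203 per group; 64 events; "we expect a mean incidence of MDD of 20% in the control group"; "we assume an absolute risk reduction of 9% with a respective hazard ratio of 0.522". The moderator sentence itself rests on no stated figure.

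**Check of the planning figures.** Risks of 20% and 11% give a hazard ratio of ln(0.89)/ln(0.80) = 0.522, as stated. Expected events are 203 × 0.20 = 40.6 in controls and 203 × 0.11 = 22.3 in the intervention group, 62.9 in total, close to the stated 64.

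**What each analysis estimates.** Let the covariate X (in SD units) have log hazard ratio b0 in controls and b1 in the intervention group.

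- Moderation is b1 − b0. Its standard error is about √(1/40.6 + 1/22.3) = 0.263.
- A covariate–outcome association adjusted for treatment estimates roughly the event-weighted average, 0.645·b0 + 0.355·b1 (weights 40.6/62.9 and 22.3/62.9). Its standard error is about 1/√62.9 = 0.126.

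The two differ in kind. With b0 = b1 the moderation is zero, while the association is the full prognostic effect.

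**Numbers.** The covariate effects are assumptions; the article gives none. For an estimate b with standard error s, the two-sided 5% detection rate is Φ(|b|/s − 1.96) + Φ(−|b|/s − 1.96). The last column gives Cox simulations with 406 participants, 20% control risk, hazard ratio 0.522 and about 65 events (400 to 2000 replicates).

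| Assumed HR per SD (controls / intervention) | Association: b, detection | Interaction: b, detection | Simulated association / interaction |
|---|---|---|---|
| 1.35 / 1.35 (prognostic only) | 0.300, 66% | 0, 5% | 66–73% / about 5% |
| 1.5 / (1/1.5) (cross-over) | 0.118, 15% | −0.811, 87% | about 16% / 85–90% |
| 1 / 1.5 (intervention group only) | 0.144, 21% | 0.405, 34% | 22–24% / 33–35% |
| 1.5 / 1 (controls only) | 0.262, 55% | −0.405, 34% | 56% / 32% |
| 1.5 / 1.2 | 0.326, 74% | −0.223, 13% | 74% / 13% |
| 1.2 / (1/1.2) (mild cross-over) | 0.053, 7% | −0.365, 28% | 7% / 30% |

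Worked example, first row: ln 1.35 = 0.300; 0.300/0.126 = 2.38; Φ(2.38 − 1.96) = 66%. The interaction is zero, so its test rejects at the nominal 5%.

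**Continuous outcome.** A simulation with 406 participants, outcome SD 1 and a binary covariate (2000 runs) gives the same reversal. A purely prognostic covariate (assumed 0.5 SD between levels) is flagged in 99.9% of runs by association and 4.0% by interaction. A pure modifier (assumed treatment effect differing by 1.0 SD between levels) is flagged in 4.5% and 99.9%.

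**Interaction power on the primary outcome.** For an evenly split binary moderator and 64 events, the standard error of the log ratio of hazard ratios is √(16/64) = 0.5. For a ratio of 0.522, |ln 0.522|/0.5 = 1.30 and power is Φ(1.30 − 1.96) = 25%. For ratios of 0.40 and 0.30 it is 45% and 67%. At 0.522, 80% power needs (1.96 + 0.842)² × 16/0.650² ≈ 298 events.

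**The case against.** The strongest reply is that this is compressed journal prose. Multiple regression is the ordinary framework for moderation and can hold interaction terms, the effect-modification purpose is stated correctly elsewhere, and an unseen analysis plan may give the model terms. That stands as a limit: the criticism applies if the sentence is carried out as written. It does not remove the point. The sentence specifies what is to be analysed, and that quantity does not measure moderation. This is a method stated wrongly, not a detail left open.

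A second reply is that interaction tests are weak here. That also stands. The cross-over of 1.5 against 1/1.5 is a favourable case for the interaction test; the milder shapes in the table give 13–34%. For some moderators the association test rejects more often (55% against 34% when the covariate acts only in controls). But such a rejection cannot be told apart from one caused by a purely prognostic covariate, so it is no evidence of moderation.

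Three stronger readings are tempting and not supported:

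- A reader might infer that identifying who benefits most is a trial objective and that implementation would be steered to the wrong patients. The remark about target populations is in the Background and describes the literature. The hypotheses at the end of the Background include none on moderation, and nothing ties implementation to moderator results.
- A reader might infer that ordinary multiple regression is being applied to the censored primary outcome. The sentence follows the one on secondary outcomes and does not say which outcome it means, so this is not established.
- A reader might infer that the moderator results are bound to be wrong. That depends on how the sentence is carried out.

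**Conclusion.** The point holds for a secondary, exploratory analysis. As written, the moderator method identifies prognostic factors and cannot separate them from effect modifiers. The outcome-association screen, if applied to candidate moderators, adds to the problem. The primary treatment comparison is unaffected.

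The firmest part of the size is false flagging: about 66–73% by association against about 5% by interaction, for an assumed prognostic hazard ratio of 1.35 per SD. This varies with the assumed strength of the covariate. For true moderators no single figure is fair: association detects from about 7% to 74% and interaction from about 13% to 90% across the assumed shapes. The case for interaction terms is therefore that they estimate the right quantity, not that they promise good power. The sentence should be corrected.

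**What to change.** Replace the moderator sentence in Clinical analyses by:

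*Potential moderators (the baseline covariates listed under Covariates) will be examined by adding treatment-by-covariate interaction terms, one covariate at a time, to the model used for the respective outcome (Cox model for time to MDD onset, hierarchical linear models for secondary outcomes). Interaction estimates with 95% confidence intervals will be reported as exploratory, given low power at about 64 events.*

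Add to the covariate selection rule:

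*This screen does not apply to candidate moderators.*

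The cost is two sentences. The data and software stay the same, and neither the sample size nor the primary analysis changes.

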**Methods:**

This study is a multicenter pragmatic randomized controlled trial (RCT) of parallel design aiming to investigate the (cost-) effectiveness of an Internet- and mobile-based intervention (IMI) for the prevention of depression in chronic back pain patients (PROD-BP) with subthreshold depressive symptoms. eSano BackCare-DP is a guided, chronic back pain-specific depression prevention intervention based on cognitive behavioral therapy (CBT) principles comprising six weekly plus three optional modules and two booster sessions after completion of the intervention. Trained psychologists provide guidance by sending feedback messages after each module. A total of 406 patients with chronic back pain and without a depressive disorder at baseline will be recruited following orthopedic rehabilitation care and allocated to either intervention or treatment-as-usual (TAU). Primary patient-relevant endpoint of the trial is the time to onset of MDD measured by the telephone-administered Structured Clinical Interview for DSM (SCID) at baseline and 1-year post-randomization. Key secondary outcomes are health-related quality of life, depression severity, pain intensity, pain-related disability, ability to work, intervention satisfaction and adherence as well as side effects of the intervention. Online assessments take place at baseline and 9 weeks as well as 6 and 12 months post-randomization. Cox regression survival analysis will be conducted to estimate hazard ratio at 12-month follow-up. Moreover, an economic analysis will be conducted from a societal and public health perspective.

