In prior studies, Internet- and mobile-based interventions (IMI) have shown to be effective in the treatment of MDD [29, 30] as well as in the treatment of subthreshold depression, indicating their potential to be utilized for preventive interventions [25, 31–34]. Human support (guidance) has repeatedly been shown to have a positive effect on effectiveness of and adherence to IMIs [35, 36].

The proposed study aims to investigate the effectiveness and cost-effectiveness of an IMI (eSano BackCare-DP) to prevent the onset of depression for chronic back pain patients (PROD-BP) with subthreshold depressive symptoms. The study will be embedded into routine orthopedic care in order to examine the intervention’s effectiveness in an unselected sample of all eligible chronic back pain patients (i.e. the implementation will not be limited to a self-selected population of people who are already attracted to depression prevention interventions and the Internet). It is expected thateSano BackCare-DP is effective in preventing the onset of MDD compared to treatment as usual (TAU) over a 12-month follow-up period,eSano BackCare-DP is cost-effective compared to TAU.Compared to TAU, eSano BackCare-DP is superior in terms of (a) depression response, (b) work capacity, (c) quality of life, (d) pain related disability and (e) pain intensity.

Furthermore, the distributions of principal confounders in each group will be explored.

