### Secondary outcomes

#### Depressive symptoms

Depressive symptoms will be assessed by the self-administered Patient Health Questionnaire (PHQ-9) [64], a telephone-based clinician rating of the Hamilton Rating Scale for Depression (HAM-D-17), and the Quick Inventory of Depressive Symptomatology (QIDS) [56, 57]. The PHQ-9 is a well validated and widely used depression screening instrument [64] and has also been evaluated to be delivered as online-version [65]. The 17-item HAM-D is the most widely used clinician-rated measure of depression severity and as such viewed as the gold standard for the assessment of depression severity. The 16-Item QIDS will be used to further validate the depressive symptom outcome measures. It covers all criterion symptom domains of the DSM for diagnosing a MDD [57]. HAM-D and QIDS are administered to determine depression response [66].

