#### Pain intensity and pain associated disability

Pain intensity and pain-related disability will be measured following the IMMPACT recommendations for core outcome measures for chronic pain clinical trials [72, 73]. Pain intensity will be measured by an 11-point numerical rating scale (0-10) of pain intensity as well as categorical classification of pain intensity (none, mild, moderate, severe). The Oswestry Disability Index (ODI) will be used to assess pain related disability. The ODI is a reliable and valid self-assessment questionnaire including 10 items [74].

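### Superiority is hypothesised on five secondary domains and every analysis is tested at .05, with no gate, order or exploratory label, so a chance secondary finding can be claimed as a benefit

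*Protocol article*

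**What the plan says.** The Background section lists what the trial expects to show. Beside effectiveness on onset of major depressive disorder (MDD) over 12 months, and cost-effectiveness, it expects that "eSano BackCare-DP is superior in terms of (a) depression response, (b) work capacity, (c) quality of life, (d) pain related disability", with pain intensity as item (e). No time point is attached to this third hypothesis.

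The Abstract (Methods) describes these outcomes as key, not exploratory: "Key secondary outcomes are health-related quality of life, depression severity, pain intensity, pain-related disability, ability to work".

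Under Clinical analyses, "Secondary outcomes will be analyzed using hierarchical linear modeling", and the threshold for significance is p "≤ .05 will be set for all analyses". The section names no testing order, no dependence on the primary result, no division of alpha, and no deciding instrument or visit for any secondary domain.

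The outcome sections and Table 1 give the measures:

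- **Depression response:** "HAM-D and QIDS are administered to determine depression response". Both are done at T0 and T3 only.
- **Quality of life:** AQoL-6D and EQ-5D-5L, at T1, T2 and T3.
- **Pain intensity:** a "numerical rating scale (0-10) of pain intensity as well as categorical classification of pain intensity", at T1, T2 and T3.
- **Pain-related disability:** the ODI only, at T1, T2 and T3.
- **Work capacity:** the SPE only, at T1, T2 and T3.

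**The concern.** A statement of superiority is normally backed by a controlled error rate. Here five such statements are made, and the only decision rule gives each of them the full .05. Read literally, one nominally significant result on pain, work capacity or quality of life satisfies a pre-stated superiority hypothesis, even if the comparison on MDD onset shows nothing.

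This goes beyond a detail that an article leaves to its analysis plan. The article states a rule for all analyses and attaches it to stated hypotheses, so an analysis plan that added a stricter secondary threshold would contradict it. The Discussion expects the results to inform health care providers and policy makers, so a chance secondary finding presented as a confirmed benefit could matter in practice.

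**Working it through.** **Inputs from the article.** Five domains (Background); threshold .05 for every analysis (Clinical analyses); measures and visits as listed above (Table 1). The article gives no familywise error figure to reproduce and no correlations between outcomes. All correlations below are assumptions and are shown as ranges.

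**Sidedness.** The article does not say whether .05 is one- or two-sided. Its sample size gives a hint. Freedman's log-rank formula is events = (z_α + z_β)² × ((1 + HR)/(1 − HR))², with HR = 0.522 and 80% power.

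- One-sided 0.05: (1.645 + 0.842)² × (1.522/0.478)² = 62.7, or 64 when rounded up to an even total. The average event probability is 1 − (0.8 + 0.8^0.522)/2 = 0.155, so N = 62.7/0.155 ≈ 404.5, rounded up to 406. Both match the article.
- Two-sided 0.05: (1.960 + 0.842)² × (1.522/0.478)² = 79.6, or 80 events and N of about 514. Neither matches.

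This is suggestive only, so both readings are carried forward.

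**One test per domain, no true effect on any domain.** For independent tests:

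- Any significant result, two-sided: 1 − 0.95⁵ = 22.6%.
- A significant result favouring the intervention, two-sided: 1 − 0.975⁵ = 11.9%.
- A result favouring the intervention, one-sided .05: 1 − 0.95⁵ = 22.6%.

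For correlated tests, simulation of five equally correlated normal test statistics (400,000 draws) gives:

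| Assumed correlation | Either direction, two-sided | Favouring intervention, two-sided | Favouring intervention, one-sided .05 |
|---|---|---|---|
| 0 | 23% | 12% | 23% |
| 0.5 | 18% | 9% | 17% |
| 0.8 | 13% | 6% | 12% |

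A single test gives 5%, 2.5% and 5% respectively.

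**Assumed worst case: every named measure at every visit.** HAM-D and QIDS at T3 give 2 tests. SPE, AQoL-6D, EQ-5D-5L, ODI, numeric pain and categorical pain at three visits give 6 × 3 = 18. The total is 20. With between-measure correlation 0.3–0.7 and between-visit correlation 0.5–0.7 (200,000 draws), a two-sided result favouring the intervention occurs in 17–29% of trials. A significant result in either direction occurs in 34–55%.

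**Effect of a correction.** Testing each of the five at 0.05/5 = 0.01 gives 1 − 0.99⁵ = 4.9% if independent, and at most 5% under any correlation. Holm keeps the same 5% bound and is never less powerful.

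**The case against.** The trial has one primary endpoint, one primary contrast and a sample size built on it alone. Calling the other outcomes secondary already ranks them lower, and unadjusted secondary tests are common in pragmatic trials with a single primary. Which instrument and visit decides each secondary is ordinary content for an analysis plan that is not shown. Much of this stands. It limits the point to the explicit all-analyses threshold combined with the stated superiority hypotheses.

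A reader might infer three stronger things that the article does not support.

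- **That every domain offers several instruments.** Only three of the five have two measures. Work capacity and pain-related disability have one each, and depression response has one post-baseline visit.
- **That a false superiority claim has a chance approaching one half.** About 48% does arise for 20 tests at assumed correlations of 0.5, but it includes results showing the intervention to be worse. Counting only results in its favour, the same case gives about 25%. The 20-test count also assumes a separate test at each visit, which the article nowhere specifies. A hierarchical linear model may give one test per outcome.
- **That the trial's main conclusion is compromised.** The error rate of the primary comparison does not depend on how the secondaries are tested.

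The Abstract's depression severity against the Background's depression response is a difference in wording and adds nothing to the multiplicity argument.

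**Conclusion.** The concern holds in a limited form: the article attaches an unadjusted .05 to five stated superiority hypotheses, with nothing to separate confirmatory from exploratory use. The main figure is the 9–12% chance of at least one false superiority claim. It assumes one two-sided test per domain, no true secondary effect and correlation between 0.5 and 0. That is roughly four to five times the 2.5% of a single test, and still more than double it at correlation 0.8. A one-sided reading would raise the range to 17–23%. The 17–29% for 20 two-sided tests is an assumed worst case. The change is worth making because it settles what the trial may claim, but it is not critical to the trial's validity.

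**What to change.** In Clinical analyses, replace the blanket threshold with wording such as: *The only confirmatory test is the primary comparison of time to onset of MDD, at the 5% level. Secondary outcomes are exploratory and are reported as estimates with 95% confidence intervals and nominal p-values; they support no claim of superiority.* State there whether the 5% is one- or two-sided. Reword the third hypothesis in the Background to match.

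If confirmatory secondary claims are wanted, test the five domains only if the primary is significant, with one named measure per domain at 12 months and the Holm procedure across the five at 5% overall. Label other measures and visits exploratory.

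Either option costs a few sentences and no extra patients or data. The downside is that a secondary p-value just under .05 can no longer be claimed as superiority. Under Holm, the smallest of the five must be at most 0.05/5 = 0.01 before any claim is made.
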